### Power analysis

We plan to include 240 participants based on a priori power analysis. With an α error level of 0.05, statistical power of 0.80, and a correlation of *r* = 0.5 between baseline and 8-week intervals, we need 174 participants (G*Power). Considering a dropout rate of 13% (based on [96]), we account for 23 participants dropping out. Additionally, given an odds ratio (OR) of 2.88 for 2-week prevalence [66], and anticipating 20% exclusion post-signing the consent form, we estimate needing 240 participants. They will be divided into three groups of 80 each (see Fig. 1).

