### The goal of the present study

The present study, registered at ClinicalTrials.gov (NCT06480474) and Swiss National Clinical Trials (SNCTP000005917), aims to investigate (1) whether Deprexis with peer-to-peer support online forums could improve the symptoms of depression as compared to Deprexis without peer-to-peer support, (2) to examine the cultural differences in the use of peer-to-peer support online forums between a non-WEIRD country (India) and a WEIRD country (Switzerland), and (3) to examine the efficacy of Deprexis in the French-speaking part of Switzerland, and to assess the effects of the online program on mood responses to monetary and social rewards in individuals with depressive symptoms in India and Switzerland.

This study has two experimental conditions (Deprexis and Deprexis with an online forum) compared with a control condition (waiting list). The control group is used to assess the difference between having access to an intervention and having no access. We expect a superiority of Deprexis and Deprexis with the online forum group against the waiting list group (control group) and a superiority of Deprexis with the online forum group against the unguided Deprexis group. Additionally, we expect higher adherence to Deprexis with the online forum. The control group will be placed on a waiting list and will have access to the program after the initial 8 weeks.

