### Trial status

The study was registered at ClinicalTrials.gov (NCT06480474) and Swiss National Clinical Trials (SNCTP000005917). The Ethics committee at the Canton of Vaud (CER-VD) approved the study in May 2024 (Protocol Date: 22.05.2024; Version: 4; 2023-D0112). Recruitment began in June 2024 and is expected to conclude in May 2026. As of August 2025, 28 participants have been recruited, of whom 9 have completed the post-intervention (T2) assessment and 6 have completed the follow-up (T3) assessment.

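### The sample size of 240 does not follow from its own stated losses, and it is used both as the number consenting and as the number randomised

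*Protocol article*

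**What the plan says.** The Power analysis section gives these inputs: "With an α error level of 0.05, statistical power of 0.80", a correlation of 0.5 between baseline and week 8, and the result "we need 174 participants (G*Power". For attrition it says "Considering a dropout rate of 13% (based on [96]), we account for 23 participants dropping out". It then cites an odds ratio of 2.88 for two-week prevalence and closes with "anticipating 20% exclusion post-signing the consent form, we estimate needing 240 participants". The next sentence splits that total into three groups of 80.

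Other sections use 240 as the number allocated. Study design gives 240 with 80 per group. Randomization assigns 240 once the inclusion criteria have been checked. Procedure randomises eligible participants into three groups of 80. The Participants section has consent signed before the eligibility screen, so people consenting and people randomised are different counts.

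The goal section expects each active arm to beat the waiting list, and also "a superiority of Deprexis with the online forum group against the unguided Deprexis group". The Abstract sets the primary outcome at 8 weeks. Trial status reports: "As of August 2025, 28 participants have been recruited, of whom 9 have completed the post-intervention (T2) assessment", with recruitment expected to end in May 2026.

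**The concern.** A total that already contains people who will be excluded before randomisation cannot also be the total randomised. Depending on which meaning the team works to, the trial stops recruiting at 192 randomised or at 240. One of these misses the stated requirement and the other exceeds it. The inflation step also fails on its own rates.

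The paragraph then claims 80% power without the quantity that determines power. A reader cannot tell what difference the trial can detect between Deprexis with the forum and Deprexis alone, which is the first stated aim and probably the smallest of the three expected differences.

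**Working it through.** **Inputs** (all from Power analysis): base requirement 174; dropout 13%, taken as 23; exclusion after consent 20%; total 240; three arms of 80; alpha 0.05; power 0.80; r = 0.5. Not stated: effect size, test, sidedness, number of measurements.

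**1. How 240 may have arisen.** 0.13 × 174 = 22.6, so the 23 is 13% of 174, and 174 + 23 = 197. Multiplying up, 197 × 1.2 = 236.4; with 197 rounded to 200, 200 × 1.2 = 240. The total is therefore approached only by multiplying by 1.2. Dividing 197 by 0.80 gives 246.

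**2. Correct inflation.** Losses are divided out: n/(1 − loss).
- 174/0.87 = 200 randomised
- 200/0.80 = 250 consenting
- For three equal arms, 201 randomised (67 each): 201/0.80 = 251.25, so 252 consenting

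**3. The two meanings of 240.**

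| 240 means | Consenting | Randomised | Completing | Against 174 |
|---|---|---|---|---|
| consented | 240 | 240 × 0.80 = 192 (64 per arm) | 192 × 0.87 = 167 | 7 below |
| randomised | 240/0.80 = 300 | 240 (80 per arm) | 240 × 0.87 = 209 | 35 above |

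**4. Can 174 be tied to a test?** Not from the stated inputs. Two sets of assumptions return it:
- Group-by-time interaction, 3 groups, 4 visits, r = 0.5, assumed f = 0.10. Noncentrality = f² × N × m/(1 − r) = 0.01 × 174 × 4/0.5 = 13.92 on 6 and 513 df; power 0.804.
- Pairwise baseline-adjusted comparison at week 8, assumed d = 0.40, one-sided 0.05. n per arm = 2 × 0.75 × (1.645 + 0.842)²/0.40² = 58, and 3 × 58 = 174. This uses the normal approximation; with the t distribution, power at 58 is 0.796.

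On the first assumption, power is 0.785 at 167 completers and 0.882 at 209.

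**5. Detectable pairwise difference at week 8**, two-sided 0.05, 80% power, equal arms, in SD units: 2.80 × √(2v/n), with v = 1 unadjusted or v = 1 − 0.5² = 0.75 baseline-adjusted.
- 58 per arm (174/3): 0.52 unadjusted, 0.45 adjusted
- about 70 per arm (209/3): 0.47 unadjusted, 0.41 adjusted

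These take the stated 80 per arm. The 1:2:2 ratio in Randomization would give 48, 96 and 96 and has to be reconciled separately.

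**6. Odds ratio.** Nothing in steps 1 to 5 uses 2.88, and the outcome is a continuous score. Its citation, [66], is the one that the secondary outcome section gives for the French BIS/BAS.

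**7. Accrual, as feasibility only.** June 2024 to August 2025 is 14 to 15 months: 28/15 × 24 = 45 to 28/14 × 24 = 48 by May 2026. The remaining 212 would need 212/10 = 21 to 212/9 = 24 per month, against about 2 so far.

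**The case against.** The best defence is that Study design, Randomization and Procedure all use 240 as the number randomised. On that reading 209 complete, the stated requirement is exceeded and no power is lost. Even on the consented reading the loss is 7 completers, under 2 points of power on the four-visit assumption. Both statements are right, and they limit the size of the problem. They do not remove the contradiction, because the paragraph that derives 240 counts the post-consent exclusions inside it.

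A second defence is that an article may leave the effect size to the full protocol, which is not shown. That is fair as far as omission goes. What stands is that the article prints a power figure that cannot be attached to any of its three superiority claims.

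A reader might infer that 174 was sized for an omnibus test over four visits, and hence not for the superiority claims. The documents do not support this. The f = 0.10 and the number of visits are assumptions found by matching to 174, and a one-sided pairwise comparison at week 8 comes to the same number. If the interaction had been used, it would agree with the group-by-time model named under Planned statistical analyses.

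A reader might also take 9 week-8 completers among 28 recruits as evidence that dropout exceeds 13%. The article does not say how many of the 28 were due at week 8, so nothing follows. Slow accrual likewise does not show that the calculation was wrong.

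**Conclusion.** The sample-size paragraph is wrong as written. On its own loss rates it needs 250 people consenting (252 for equal arms), so 240 is 10 to 12 short as a consent target. As a randomisation target, 240 is more than sufficient for 174 completers but implies about 300 consents, which the article does not state. These results rest only on the printed 174, 13% and 20%.

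The odds ratio has no function. The test behind 174 is unknown, so the 80% power belongs to no identified comparison. The detectable differences of 0.41 to 0.52 SD assume equal arms, two-sided testing at 0.05 without multiplicity adjustment and, where adjusted, r = 0.5.

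The effect on power is minor: 0.785 against 0.804 if 240 means consented, under the assumed four-visit test, and none if it means randomised. The documents therefore do not show an underpowered design, only a total that is mis-derived and ambiguous. The projection of about 45 to 48 recruits is a separate feasibility remark and assumes a constant rate.

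**What to change.** Rewrite the Power analysis paragraph:

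1. State whether 240 is the number consenting or the number randomised, and correct the other figure: either 250 to 252 consenting for 174 completers, or 240 randomised with about 300 consenting. Use the same meaning in every section.
2. Delete the odds ratio and its citation.
3. Name the test, sidedness and effect size that gave 174.
4. Give the detectable pairwise PHQ-9 difference at week 8 for the number expected to complete, in particular for forum versus Deprexis alone.
5. In Trial status, restate the expected total, end date and resulting power at the accrual observed.

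The cost is mostly wording. If 240 was meant as the consent target, keeping 174 completers takes 10 to 12 more consents. If it was meant as the randomisation target, the roughly 300 consents are already implied by the plan and only need to be stated.

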### Planned statistical analyses

The analysis will be done with the help of appropriate software programs (e.g., JASP or SPSS) by the end of the study. It will be conducted on the Intention-To-Treat (ITT) sample. Before analysis, all outcome variables will be tested for normality using the Kolmogorov-Smirnov test and, if necessary, transformed to obtain a normal distribution. To test for the main and interaction effects of treatment components on primary and secondary outcomes, a linear mixed-model repeated measures ANOVA with time as a within-groups factor and treatment condition as a between-groups factor will be used for the main research question. Also, repeated measures ANOVA will be used to test the effects of Deprexis on reward responses and on perceived social support in relationship to the forum utilization. We will also use mediation analyses to test our objectives. If the questionnaires have more than 30% of the missing data, they will not be used in the analysis, and for the other cases, missing data will be computed with the help of the statistics software. Interim analysis will be performed for preliminary data presentation at scientific meetings and to check data quality.

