**Methods:**

The study is a randomized controlled trial; participants with mild to moderate depression will be randomized into three groups of 80 each: Deprexis only, Deprexis with peer-to-peer support, and a control group on a waiting list. The intervention lasts 8 weeks, with measurements at baseline (T0), mid-intervention (4 weeks, T1), post-intervention (8 weeks, T2), and follow-up (3 months post-intervention, T3). Participants will complete online questionnaires on RedCap and the Fribourg Reward Task. Primary outcome: depressive symptoms at 8 weeks post-intervention. Secondary outcomes: mood responses to reward, pleasure, and social support, with moderators and mediators like anxiety, stress, quality of life, PTSD, childhood trauma, self-efficacy, and self-esteem.

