### Participants

Participants will be recruited through flyers and emails, word-of-mouth, social media (e.g., Facebook, Instagram), depression-related websites, private psychotherapists, outpatient clinics in French-speaking Switzerland, and the English-speaking population from India. Interested participants will receive information on the study, and then they will be given at least 24 h to confirm their participation by signing and returning the informed consent of the study (via email). They will be screened to assess eligibility using a rapid eligibility check, using the inclusion and exclusion checklist and the Patient Health Questionnaire (PHQ-9; [57]).

The inclusion criteria are (1) providing signed informed consent; (2) being at least 18 years of age; (3) having access to a computer/laptop/tablet/smartphone with an internet connection; (4) having sufficient French language skills in Switzerland and English in India; (5) meeting criteria for mild to moderate depression as operationalized by the Patient Health Questionnaire-9 (PHQ-9 = 5–14) (PHQ-9; [57]) meeting the diagnostic criteria of the characterized depressive disorder according to the diagnostic interview by telephone; and (7) providing the emergency contact before treatment.

However, they will be excluded from the study if they present any of the following criteria: (1) having active suicidal plans (if they have a score of 2 or higher on the suicide item of the PHQ-9 [57] or with active suicidal plans in the diagnostic telephone interview; (2) having a history of psychotic disorder or bipolar disorder; and (3) changing their dosage of prescribed medication for anxiety or depression in the last month before the study. When potential participants fulfill inclusion criteria, they will be interviewed by telephone for screening using the MINI International Neuropsychiatric Interview (M.I.N.I; [58]). The current protocol is prepared in accordance with the “Standard Protocol Items: Recommendations for Interventional Trials (SPIRIT) 2013” guidelines [59].

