#### Primary outcome measures

Patient Health Questionnaire (PHQ-9; English version [62]; French version [57]). This self-reported measure is used in several RCT studies to assess depressive symptoms [34, 36]. The PHQ-9 is a valid, reliable, and useful tool for clinical and research purposes.

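### The Kolmogorov-Smirnov check on raw outcomes tests the wrong quantity, tends to fire because PHQ-9 is a whole-number score, and leaves the primary analysis scale to be chosen from the data

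*Protocol article*

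**What the plan says.** Under Planned statistical analyses the protocol article states that, before analysis, "all outcome variables will be tested for normality using the Kolmogorov-Smirnov test and, if necessary, transformed to obtain a normal distribution". The same paragraph then names the main model: "a linear mixed-model repeated measures ANOVA with time as a within-groups factor and treatment condition as a between-groups factor will be used".

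The abstract gives the endpoint as "Primary outcome: depressive symptoms at 8 weeks post-intervention", and the section on primary outcome measures names PHQ-9 as the instrument. Nothing exempts PHQ-9 from the normality step or fixes the scale on which it is analysed.

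The article gives no PHQ-9 mean or SD. Its only statement about the distribution is the entry range under Participants: "meeting criteria for mild to moderate depression as operationalized by the Patient Health Questionnaire-9 (PHQ-9 = 5–14".

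**The concern.** Three things are wrong with the rule as stated.

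- **Wrong quantity.** The linear mixed model relies on approximately normal residuals, given arm, visit and the other model terms. Whether the raw outcome passes a normality test says little about that.
- **A trigger unrelated to the model.** The Kolmogorov-Smirnov (K-S) statistic compares a step function with a smooth normal curve. A whole-number score has large steps, so the test can reject even when the underlying quantity is exactly normal. A monotone transformation keeps the same ties, so it cannot remove this cause.
- **A scale left open.** If the test is followed, the primary analysis may be in PHQ-9 points or in transformed units, depending on the data. The main question is a time-by-condition effect, and an interaction can appear or vanish when the scale changes. A transformed effect is also not in PHQ-9 points, which makes it hard to interpret or to compare with other trials.

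**Working it through.** **1. Sample sizes the test would see.** The Power analysis section says "we need 174 participants (G*Power" and "Considering a dropout rate of 13% (based on [96]), we account for 23 participants dropping out".
- 174 × 0.13 = 22.6, rounded to 23.
- 174 / 0.87 = 200, and 200 × 1.2 = 240, the planned total. (Using 174 + 23 = 197 instead gives 197 × 1.2 = 236.4.)
- Per arm: 174 / 3 = 58 and 240 / 3 = 80.

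The article does not say whether testing is pooled or per arm, so n = 80, 174 and 240 are all relevant.

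**2. Why ties matter.** Rounding a normal variable with SD s to whole points separates the step function from the normal curve by about half the probability of the commonest score, that is 0.5 × 0.399 / s. With an assumed s = 4 this is 0.5 × 0.399 / 4 = 0.05. The gap does not shrink as n grows, but the critical value falls as 1/√n: from n = 80 to n = 240 it falls by a factor of √(240/80) = 1.73. Larger samples therefore make rejection more likely without any change in the data's shape.

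**3. How often the test fires.** Simulation, 1000 data sets per case, 5% level. Means, SDs and the 0–27 range are assumptions.

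| Scores | Test | n = 80 | n = 174 | n = 240 |
|---|---|---|---|---|
| Continuous normal (control) | Lilliefors | 4% | 4% | 3% |
| | Uncorrected | 0% | 0% | 0% |
| Normal(10, SD 4), rounded, no bounds | Lilliefors | 30% | 80% | 95% |
| | Uncorrected | 1% | 6% | 14% |
| Week 8, rounded and limited to 0–27, mean 6–8, SD 4–5 | Lilliefors | 25–47% | 69–94% | 90–100% |
| | Uncorrected | 0–1% | 3–15% | 9–40% |
| Week 8, skewed (negative binomial, mean 7–8, variance 20) | Lilliefors | 84–91% | 100% | 100% |
| | Uncorrected | 15–26% | 80–92% | 97–100% |

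A separate simulation of plausible week-8 scores gave about 31%, 80% and 97% (Lilliefors) and about 1%, 8% and 17% (uncorrected), inside the ranges of the third case. The first two cases differ in rounding, and the Lilliefors rate at n = 240 goes from 3% to 95%. The Lilliefors routine used rejects only 3–4% of truly normal data, so an exact 5% version would fire somewhat more often.

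**4. What the choice of scale does.** Simulation of 2000 two-arm trials, 80 per arm. Baseline is a whole number limited to 5–14 (a simplification), and week 8 = 3 + 0.6 × baseline + effect + normal noise (SD 4), rounded and limited to 0–27. The analysis is a baseline-adjusted linear model, a simple stand-in for the planned mixed model.

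| | Raw | Square root | log(1 + x) |
|---|---|---|---|
| Type I error | 0.059 | 0.057 | 0.052 |
| Power, assumed 2-point effect | 0.87 | 0.86 | 0.83 |

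The Monte Carlo standard error of the type I error is √(0.05 × 0.95 / 2000) = 0.005, so 0.059 is within two standard errors of 0.05. Raw and log scales gave different significance verdicts in 4.7% of null trials and in 8.8% of trials with the 2-point effect.

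**The case against.** The best defence has several parts, and most of them limit the point without removing it.

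- **The rule is not automatic.** The text transforms only where judged necessary and sets no p-value that forces it. This stands. It also means that judgement after seeing the data can decide the scale.
- **The baseline is not truncated at 5–14.** A reader might infer from the entry range that baseline scores are cut and so bound to fail. The range applies to the screening PHQ-9, and Table 1 shows a separate PHQ-9 at T0. Simulating T0 after such screening (assumed mean 10, SD 4.5, correlation 0.6–0.85) gives Lilliefors rejection of 31–52% at n = 80 and 80–97% at n = 174, and uncorrected rejection of 0.3–2% and 5–13%. The restriction acts on T0 only softly.
- **A working treatment does not trigger the test.** A reader might argue that pooled arms form a non-normal mixture. That is true formally, but with continuous normal arms 2 to 4 points apart and SD 4–5 the corrected test rejects about 4%, no more than nominal.
- **Different scales at different visits.** Nothing in the text suggests that T0, T1 and T2 would be transformed differently within one model.
- **Detail may sit elsewhere.** The K-S version, the unit tested and the transformation may be fixed in an analysis plan not shown, and their absence here is no fault. The decision to pre-test raw outcomes is stated in the article and can be judged as it stands.

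**Conclusion.** The point holds as a recommended change of modest consequence. The article states a normality gate on raw outcomes, including the primary one, where the model calls for a look at residuals. Whole-number scoring alone makes the Lilliefors-corrected test likely to reject at the pooled planned sizes (about 80% at n = 174 and 97% at n = 240 for week-8 scores). The uncorrected version would usually pass the same scores (about 8% and 17%), unless they are clearly skewed. The outcome of the check thus depends heavily on which version is run.

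A reader might infer that the trial's error rates are compromised. The working does not support that: type I error is close to nominal on all three scales and power differs by at most 0.04. The harm is a primary scale open to choice from the data, an interaction that can depend on it, and a result not in PHQ-9 points. The same near-nominal error on the raw scale shows that the gate is not needed.

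All simulated rates rest on assumed PHQ-9 means, SDs, shapes and range. The direction is stable across the cases tried, but the exact percentages are not.

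**What to change.** Delete the K-S test and transformation step for PHQ-9. State that the primary analysis uses original PHQ-9 points at every visit, that model residuals will be checked graphically, and that one pre-named sensitivity analysis (for example bootstrap or robust intervals) will be reported whatever the residuals show. The same wording can serve the secondary questionnaire scales.

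This is a change of wording that removes a step from the analysis. It is best made now: the Trial status section reports only 9 participants with a completed T2 assessment as of August 2025, so the scale can still be fixed before most of the primary outcome data exist.

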#### Secondary outcome measures

##### Fribourg reward task

In parallel, participants will be asked to complete an online reward task, to measure reaction times, accuracy, and mood reactions to both monetary and social rewards. For this, we will use an online adapted behavioral version of the Fribourg reward task [46–48]. This task was originally programmed using E-Prime software (version 1.1.3, Psychology Software Tools Inc., Pittsburg, Pa., USA) and made available online using OpenSesame, a graphical experiment builder for the social sciences. The experimental task was presented in three block conditions, comprising reward conditions (monetary reward, social reward, and no reward). For this task, there are three conditions (monetary reward, social reward, and no reward). Each condition consists of 12 trials, and the order of the blocks was pseudo-randomized. In the three-reward conditions, at the onset of each trial, a visual cue (2000 ms) was presented (3 yellow circles), along with the reward associated with performance. After the presentation of a fixation cross (500 ms), participants saw an array of yellow circles (3 circles, 2000 ms). A fixation cross (3000 ms) was presented before the visual target. The visual target (a green circle, 3000 ms) was displayed in any position on the screen and signaled that the participant should decide as quickly as possible whether this circle was in the same position as one of the circles presented previously. After response execution and a variable jittered interstimulus interval (ISI; 0 ms or 2000 ms), the feedback screen (1500 ms) informed the participant of their winnings. In each condition, the way correct and incorrect trials are presented differs as follows:In the social reward condition: a neutral face is presented for incorrect trials and a smiling face for correct trials.In the monetary reward condition: a screen with “CHF 0” is shown for incorrect trials and “CHF 1” for correct ones.In the control condition: a blank screen is presented in both correct and incorrect trials.

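### Reward responses and perceived social support fall under both the linear mixed model and a separate repeated-measures ANOVA; the plan should name one mixed model on all available sessions as the deciding analysis

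*Protocol article*

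**What the plan says.** All references are to the protocol article.

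- **Population** (Planned statistical analyses): "It will be conducted on the Intention-To-Treat (ITT) sample".
- **First analysis** (same section): "To test for the main and interaction effects of treatment components on primary and secondary outcomes, a linear mixed-model repeated measures ANOVA" is planned. Its only factors are time and treatment condition, and the sentence ends by tying it to the main research question: "treatment condition as a between-groups factor will be used for the main research question".
- **Second analysis** (next sentence): "repeated measures ANOVA will be used to test the effects of Deprexis on reward responses and on perceived social support", the latter in relation to forum use.
- **Status of the outcomes** (Abstract, Methods): "Secondary outcomes: mood responses to reward, pleasure, and social support". The body also lists the Fribourg Reward Task and the social support scale under secondary outcome measures.
- **Missing data** (Planned statistical analyses): questionnaires with more than 30% missing are left out. For other cases, missing values are to be computed by the software, and no method is named.
- **Task sessions**: Table 1 marks the reward task at T0, T1 and T2. The adherence paragraph under Procedure pays task winnings at T0 and T2 only, up to CHF 24.

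**The concern.** Two analyses are written for the same secondary outcomes, and the text does not say which one decides. If they differ in model and in sample, the choice can be made after the results are known. The same section also plans interim analyses for presentation at meetings, so results may be seen before the choice is settled.

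The two methods also treat incomplete data differently. A likelihood-based mixed model uses every session a participant attended. A classical repeated-measures ANOVA on wide data needs every within-person cell. For this task that means each scheduled visit crossed with three reward conditions. Missed sessions must then either remove the participant or be filled in beforehand. Removal does not fit the ITT statement. Filling in depends on a rule whose wording starts from questionnaires, whereas the task is behavioural. If values are imputed only once and then treated as observed, standard errors come out too small.

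Finally, the mixed model as written has no reward-type factor, although the stated aim concerns monetary and social reward.

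**Working it through.** **1. Do the two sentences overlap?** The first covers primary and secondary outcomes. The second covers reward responses and perceived social support, both secondary. The overlap is therefore in the text itself. Nothing ranks the two analyses.

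**2. The plan's own sample-size figures.** The article gives 174 participants, 13% dropout and a total of 240. 174/0.87 = 200, and 200 × 1.2 = 240. The 174 is reproduced by a 3-group, 4-visit within-between interaction with r = 0.5 and an assumed effect size f = 0.10 (power 0.804 at 174, 0.796 at 171). The article states neither f nor the number of visits used. These figures do not settle the model question; they supply the 13% and the r = 0.5.

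**3. How many would be complete?**
- 13% dropout alone: 240 × 0.87 = 208.8, about 209 (69.6 per arm of 80).
- A further 10% missing T1 (assumption): 208.8 × 0.90 = 187.9, about 188 (62.6 per arm).

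**4. Precision lost by complete-case analysis.** Take the T0-to-T2 change in one arm of n, with unit variance at each visit and r = 0.5 between all visits. The article states 0.5 for baseline to 8 weeks; applying it to the reward contrast is an assumption. The variance of a change is 2(1 − r) = 1.

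- *Complete cases, 13% lost:* 1/(0.87n) = 1.149/n.
- *All available data, dropouts seen at T0 and T1:* regressing the change on T0 and T1 leaves residual variance 2/3 and explains 1/3. The variance is (2/3)/0.87 + 1/3 = 0.766 + 0.333 = 1.100, over n. Ratio 1.149/1.100 = **1.05**.
- *All available data, dropouts leave before T1:* residual 0.75, explained 0.25. The variance is 0.75/0.87 + 0.25 = 1.112, over n. Ratio 1.149/1.112 = **1.03**. The same ratio applies if the task is run only at T0 and T2.
- *A further 10% independently missing T1 (assumption):* complete cases give 1/(0.87 × 0.90) = 1/0.783 = 1.277, over n. All available data, combining the information from the four attendance patterns (proportions 0.783, 0.087, 0.117 and 0.013), give 1.101, over n. Ratio 1.277/1.101 = **1.16**. With 80 per arm, the standard errors of the arm difference are √(2 × 1.277/80) = 0.179 and √(2 × 1.101/80) = 0.166.

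**5. Bias.** Simulations with T2 dropout depending on the T1 value in one arm (r = 0.5, no true effect, 80 per arm) gave mean estimates within 0.01 of zero for both approaches. The cost shown is precision only.

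**6. Is there a T1 task session?** Table 1 says yes. The payment cap of CHF 24 equals 12 trials × CHF 1 × 2 sessions, using the CHF 1 shown on the feedback screen, and so fits payment for two sessions. Either the T1 session is run without winnings or the two places disagree. The 16% figure requires a T1 session.

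**The case against.** The strongest reply is that there may be only one model. The first analysis is itself called a mixed-model repeated measures ANOVA, so the shorter name in the next sentence may be shorthand for it. The first is also tied to the main research question, and the second may simply be where reward type enters. This cannot be excluded. Against it, the second sentence opens with a word of addition, drops the mixed-model label and names outcomes already covered. If it is shorthand, a single line of clarification settles the point.

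A reader might infer that the plan discards anyone who misses a session and so breaches ITT. The document does not say that. It provides for missing values to be computed, and the phrase about other cases can be read to include the task. The ITT conflict is therefore conditional: it arises only if the ANOVA is classical and task sessions are not filled in.

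A reader might also take 16% as the cost. That depends on a T1 loss the article does not give and on a T1 session that is itself uncertain.

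One might also want block order in the model. Block order is pseudo-randomised and mood is rated before and after each block, so a constant drift cancels from the reward-minus-no-reward contrast in change scores. No case for that adjustment is made here.

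A full analysis plan may well specify factors and missing-data handling, and their absence from an article is not the criticism. What stands is that the article names two analyses for the same outcomes and leaves their relation open.

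**Conclusion.** The point holds as an overlap in the stated analyses. Reward responses and perceived social support come under the mixed model and also under a repeated-measures ANOVA, with no deciding analysis. Read as a classical ANOVA, the second is the weaker method on either route. On complete cases it gives up about 3 to 5% in variance at the protocol's 13% dropout, and about 16% if a further 10% miss T1. On filled-in values it rests on an unnamed method, and standard errors would be too small if values were imputed once.

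These sizes assume r = 0.5 for the reward contrast and 80 per arm. No bias has been shown, and neither the primary outcome nor the sample size is affected. The change is worth making because it removes a choice between analyses and costs almost nothing.

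**What to change.** - Replace the repeated-measures ANOVA for the reward task with one linear mixed model, named as the deciding analysis, fitted to all available sessions. Outcome: mood after minus mood before each block. Fixed effects: arm, visit, reward type and their interactions. Random effect: participant.
- Name the test: the arm difference at T2 in the reward-minus-no-reward contrast, once for monetary and once for social reward.
- Use the same mixed-model approach for perceived social support, including the analysis in relation to forum use.
- Say how missed task sessions are handled, separately from the questionnaire rule.
- Reconcile Table 1 (task at T0, T1 and T2) with the adherence paragraph under Procedure (task winnings at T0 and T2).

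Cost: wording in the analysis plan and one reconciliation. No analysis item needs new data, and mixed models run in the software the article names as examples.
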